#### Data Collection

Self-report data will be collected from caregivers through electronic quantitative surveys administered via REDCap (3 times total) and one-time qualitative interviews.

#### Quantitative Measures

##### Parenting Stress

The 90-item Stress Index for Parents of Adolescents [57] assesses caregivers’ perception of stressful areas in caregiver-adolescent interactions, including the relationship between stress and adolescent-caregiver characteristics, the quality of adolescent-caregiver interactions, and stressful life circumstances.

##### Mindful Parenting

The 8-item Interpersonal Mindfulness in Parenting Scale [58] assesses present-centered emotional awareness in parenting, present-centered attention in parenting, nonreactivity or low reactivity in parenting, and nonjudgmental acceptance in parenting.

##### Parenting Self-Efficacy

The 20-item Parenting Self-Efficacy Scale [59,60] assesses caregivers’ perceived parenting ability across 3 dimensions: parental connection, behavioral influence, and psychological autonomy.

##### Adolescent Services Use

The Child and Adolescent Services Assessment [61] obtains information about service use for mental health and substance use needs across multiple sectors (eg, schools and the legal system), including details about the type of treatment facility, professional discipline of provider(s), outpatient services, and out-of-home placements. We adapted this instrument to also assess whether services were mandated by the legal system. Outcomes of focus will include whether the adolescent completed any behavioral health services following release into the community (yes or no) and whether they complied with mandated services (yes or no). Barriers to adolescent services are also assessed (16 barriers; language, transportation, cost, stigma, etc). The assessment focuses on the 3 months before the adolescent’s detention (at baseline) and for follow-ups in the 3 months since the last assessment.

##### Motivation for Youth’s Treatment

The 8-item Motivation for Youth’s Treatment Scale [27] assesses intrinsic motivation for youth treatment through 2 subscales: (1) recognition that the youth has a problem and (2) readiness to participate in the youth’s treatment.

##### Caregiver Behavioral Health

The 23-item DSM-5 Level One Cross Cutting Symptom Inventory [62] assesses psychiatric symptoms (depression, anxiety, mania, psychosis, etc) and substance use during the past 2 weeks.

##### Acceptability of the RAISE App

For caregivers randomized to the RAISE condition only, the 18-item mHealth App Usability Questionnaire for Standalone mHealth Apps [63] assesses the acceptability (ie, ease of use, interface and satisfaction, and usefulness) of the RAISE app.

##### Sociodemographic Characteristics

We will collect data on caregiver race, ethnicity, gender, education, income, and adolescent history of legal involvement.

##### Application Use Metrics

We will extract use metrics from the Chorus platform. Metrics will include the number of days of use, number of modules completed, time spent practicing mindfulness exercises, and responses to self-monitoring messages sent by the application.

#### Qualitative Interviews with Caregivers

All caregivers (both conditions) will be invited to participate in a one-time qualitative interview at the time of the 3-month follow-up assessment. Interviews will focus on the feasibility, acceptability, and satisfaction with the RAISE app and informational brochure conditions (Multimedia Appendix 4).

#### Statistical Analysis

##### Quantitative Analysis

Analyses will be conducted using IBM SPSS Statistics software. Descriptive statistics will be used to examine issues related to recruitment (eg, sufficient numbers of caregivers consenting and pace of recruitment), randomization (eg, whether participants are willing to be randomized), assessment (eg, valid, reliable, acceptable, and complete), and retention (eg, rates of follow-up assessment completion). Preliminary analyses will examine whether the randomization process was successful, comparing groups on multiple background (gender, race, etc) and baseline (parenting stress, caregiver mental health, etc) variables through independent samples *t* tests (continuous variables) and chi-square analyses (categorical variables). If there are group differences, subsequent analyses will be run both with and without accounting for these variables. Efforts will be made at each stage of analysis to assess the importance of race and gender. Initially, means, distributions, and reliabilities for all major measures will be examined separately by race and gender. Any observed differences across demographic subgroups will be considered in the interpretation of substantive analyses. The proportion of missing data will be examined before outcome analyses to determine whether a complete case analysis is appropriate or whether multiple imputation is warranted (eg, if there is a large proportion of missing data, ie, >5%; if there are patterns in missingness based on demographic factors) [64].

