**Methods:**

A randomized controlled trial with 60 caregivers of detained adolescents (ages 12-17 years) across the United States will be conducted. Caregivers will be recruited through passive and active techniques and randomized to receive RAISE (intervention) or an informational brochure (comparison). Self-assessment questionnaires will be completed at baseline and 3- and 6-month follow-up timepoints. The fully automated RAISE intervention includes an 8-week stress reduction intervention, self-monitoring and affirmational SMS text messaging, and resources related to navigating the juvenile legal system. Assessments include empirically validated measures of parenting stress, mindful parenting, parenting self-efficacy, adolescent services use, motivation for youth treatment, caregiver behavioral health, sociodemographics, and RAISE usability (intervention only). Caregivers will also participate in a semistructured qualitative exit interview at the 3-month (postintervention) timepoint. Descriptive statistics will examine recruitment, randomization, assessment, retention, and application usability. Independent samples *t* tests and chi-square analyses will determine whether randomization was successful based on multiple background variables; group differences will be accounted for in outcome analyses. Regression analyses will be used for outcome analyses, with an intent-to-treat design; analyses will include intervention group as a predictor and control for the baseline level of the outcome, application usage, and demographic characteristics. Potential moderators and mediators of intervention effects will be explored.

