### Study Sample Size Determination

The main overall study focus is on the feasibility and acceptability of the codevelopment process and RAISE intervention; however, we will examine the direction of effects through this pilot RCT and cautiously consider effect size to inform sample size determination for a subsequent phase 2 efficacy trial. As with most pilot studies, these analyses are underpowered (for primary analyses considering a sample of 60 participants with α=.05, 4 of predictors, and estimating a medium effect size (Cohen f^2^=.15), power=.62). There are notable concerns with calculating effect sizes based upon pilot studies, including potential for overestimating and underestimating effects [52]. Given that we anticipate small to medium effect sizes, we followed published guidance to determine a planned enrollment of 30 participants per study arm [53].

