### Randomization

Participants will be randomized (using the REDCap [Vanderbilt University] randomization module [55,56]) to either the RAISE intervention group (30/60, 50%) or the informational brochure comparison group (30/60, 50%) directly after consent and completion of the baseline assessment. Randomization is blocked (to avoid “runs” of assignment to the same condition) and stratified by gender to ensure balance between the 2 conditions (because most caregivers are anticipated to identify as women). The randomization table is generated by a biostatistician and is not visible to the research assistant before assignment; no blinding was used. Participants will not be told which condition is the intervention of interest, but during the informed consent discussion are informed that they may be invited to test a mobile app.

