#### RAISE Effectiveness

Outcome analyses will focus on proximal caregiver-level outcomes, including mindful parenting, parenting stress, parenting self-efficacy, perceived barriers to youth treatment, and motivation for youth treatment. Secondary distal outcomes will include adolescent treatment initiation and retention. Linear regression will be used for continuous outcomes (ie, mindful parenting, parenting stress, perceived barriers to youth treatment, motivation for youth treatment), logistic regression for 3- and 6-month follow-up dichotomous outcomes (ie, treatment initiation and adherence to mandated treatment), and Poisson or negative binomial regressions for count outcomes (ie, number of treatment sessions attended). All analyses will include the intervention group as a predictor and control for baseline level of the outcome variable, application usage, and demographic characteristics (determined during preliminary analysis). Potential moderators and mediators of intervention effects will be explored using the PROCESS macro in SPSS, which uses a regression framework. Moderation analyses will involve computing interaction terms of intervention group (intervention vs comparison) by key demographic factors (eg, caregiver age, gender, race, mental health, substance use, and youth age, centered before computing interaction term for continuous variables). Mediational effects will examine the impact of intervention group on key proximal outcomes assessed at 3 months (ie, mindful parenting, parenting stress, parenting self-efficacy, perceived barriers to youth treatment, and motivation for youth treatment) and their impact on distal youth treatment engagement and retention outcomes assessed at 6 months. An “Intent to Treat” design, where all initially assigned to the intervention group are included in analyses, whether or not they used the intervention, will be used.

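### Additional covariates are chosen by baseline significance tests while the stratification factor, gender, is not fixed in the model, so the adjusted estimate depends on chance imbalance and neither of two versions is named as main

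*Protocol article*

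**What the plan says.** - **Quantitative Analysis.** The arms are compared on several background and baseline variables, gender and race among them, "through independent samples *t* tests (continuous variables) and chi-square analyses (categorical variables". The stated purpose is to judge whether randomization worked. The consequence is: "If there are group differences, subsequent analyses will be run both with and without accounting for these variables". The number of variables and the significance threshold are not given.
- **RAISE Effectiveness.** All outcome models contain the intervention group and control for the baseline level of the outcome, application usage, and "demographic characteristics (determined during preliminary analysis").
- **Abstract, Methods.** The tests "will determine whether randomization was successful based on multiple background variables; group differences will be accounted for in outcome analyses". No unadjusted version is mentioned.
- **Randomization.** Allocation is blocked and "stratified by gender to ensure balance between the 2 conditions". Most caregivers are expected to be women. No section fixes gender as a covariate. It appears as a balance-tested variable, a descriptive subgroup and a possible moderator.

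**The concern.** A biostatistician generates the allocation table and it is applied through REDCap. If that process works, every baseline difference between arms is due to chance, and a significance test cannot show whether randomization succeeded.

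As a way of choosing covariates, the tests use the wrong criterion. A variable matters for adjustment if it predicts the outcome, not because it crossed a threshold between arms. Gender shows the problem: the design balances it deliberately, so a rule based on imbalance will rarely pick it, although the stratification factor belongs in the model by design.

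The two analysis sections also give different instructions: one runs models with and without the flagged variables, the other controls for the selected characteristics in all models. An outcome can therefore have two estimates, and the text names neither as main. This matters because Study Sample Size Determination says effect sizes will be considered, cautiously, when sizing a later efficacy trial.

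**Working it through.** **1. The plan's own power figure.** Inputs from Study Sample Size Determination: "for primary analyses considering a sample of 60 participants with α=.05, 4 of predictors" and "estimating a medium effect size (Cohen f^2^=.15), power=.62". As an overall regression F test, the numerator df is 4, the denominator df is 60 − 4 − 1 = 55, and the noncentrality is 0.15 × 60 = 9. Power is 0.621, so the stated 0.62 reproduces. The calculation fixes four predictors, but the analysis rule does not. Group, baseline outcome and application usage make three if usage is one variable, which leaves 4 − 3 = 1 place for demographics. The number selected is left to the data.

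**2. How often chance triggers the rule.** For k independent tests at 5%, the probability of at least one significant difference is 1 − 0.95^k. Both k and the 5% level are assumptions.

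| k | 1 − 0.95^k |
|---|---|
| 5 | 22.6% |
| 8 | 33.7% |
| 10 | 40.1% |

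**3. Would the rule select gender?** Assume 85% women: 51 women and 9 men among 60. If each stratum splits as evenly as possible, the arms hold 26 women and 4 men against 25 women and 5 men. Chi-square = 60 × (26 × 5 − 25 × 4)² / (30 × 30 × 51 × 9) = 54,000 / 413,100 = 0.13, against a 5% critical value of 3.84. The block size is not stated, so the real split could be less even, but the direction is clear.

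**4. What the rule does to the estimate.** Simulation with no intervention effect: 10,000 trials per setting, n = 60, 1:1 allocation stratified by gender. Assumed: 85% women, a baseline–outcome correlation of 0.5, and eight independent candidate covariates tested at 5%. Both versions adjust for the baseline outcome. One also adds the flagged covariates. If nothing is flagged, the two are the same.

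| Coefficient of each covariate (SD) | Rule triggered | Type I error without | with | either | either, triggered trials only | Mean absolute difference between the two estimates, triggered trials (SD) |
|---|---|---|---|---|---|---|
| 0 | 33.0% | 4.9% | 5.0% | 5.55% | 6.5% | 0.06 |
| 0.20 | 32.9% | 5.0% | 4.0% | 5.64% | 9.2% | 0.13 |
| 0.25 | 33.9% | 4.9% | 3.2% | 5.33% | 9.2% | 0.16 |

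The simulation error on a 5% rate is √(0.05 × 0.95 / 10,000) = 0.2 percentage points.

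For scale, the standard error of the group difference with 30 per arm and a baseline correlation of 0.5 is about √(2/30) × √(1 − 0.25) = 0.258 × 0.866 = 0.22 SD. The two versions thus differ on average by 0.06 / 0.22 to 0.16 / 0.22, or roughly 0.3 to 0.7 of a standard error.

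**5. Cost of fixing gender in the model.** For a 1-df test of the group term at f² = 0.15 and N = 60, power is 0.838 with four predictors and 0.838 with five (noncentrality f² × N). With noncentrality f² × denominator df it is 0.806 and 0.798. This shows only that one more term costs almost nothing. It does not correct the 0.62, which is for a different test.

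**The case against.** The strongest reply has four parts.

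- **The harm is small and the trial is a pilot.** The article says its main focus is feasibility and acceptability, that the analyses are underpowered, and that effect sizes will be treated cautiously. This stands and limits the weight of the point. A reader might take the 23% to 40% as a false-positive rate for RAISE. It is only the chance that the rule is triggered.
- **The main prognostic variable is already fixed.** A reader might infer that the whole model is data-driven, or that the fix would bring the precision gain from baseline adjustment. Neither holds: RAISE Effectiveness already puts the baseline outcome and application usage in every model. The data-dependence concerns only the additional demographic and background covariates.
- **Naming a primary model can be left to an analysis plan that is not shown.** That is fair as far as omission goes. The point here rests on a stated selection rule and on two sections that give different instructions. Showing both versions is a reasonable sensitivity check once one is designated as main. The abstract's wording may be mere condensation, so the real tension is between the two analysis sections.
- **Gender may still get in.** The article promises attention to race and gender at each stage and lists gender as a moderator. It also does not say outright that the demographic covariates are picked by significance alone, although the balance tests are the preliminary analysis it describes. What it specifies for gender is descriptive or exploratory, so gender is still not fixed in the main model. A reader might infer that leaving it out biases the result. In a linear model, omission typically leaves the estimate unbiased and the standard error somewhat conservative.

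**Conclusion.** The point holds in a limited form. The article uses baseline significance tests to decide on additional covariates, does not fix the stratification factor, and gives two rules that can yield two estimates per outcome with neither named as main.

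With 5 to 10 independent tests at 5%, chance triggers the rule in about 23% to 40% of trials. In the simulated settings the two estimates then differ by 0.06 to 0.16 SD on average. If either could be reported, the false-positive rate is 6.5% to 9.2% in triggered trials but only about 5.3% to 5.6% over all trials. These figures rest on the assumed number, independence and threshold of the tests and on the assumed correlations; the article gives none of these.

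The case for change is therefore not serious error inflation. It is that one pre-specified estimate per outcome is better, and almost free, in a pilot that will inform the size of the next trial.

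**What to change.** 1. Describe baseline characteristics by arm, and do not use t tests or chi-square tests to select covariates or to judge whether randomization worked.
2. Pre-specify one main model per outcome: group, baseline value of the outcome (already planned), gender as the stratification factor, and at most one or two prognostic baseline variables named before outcomes are compared by arm.
3. Label any other adjusted or unadjusted model a sensitivity analysis.
4. Make the abstract, Quantitative Analysis and RAISE Effectiveness state this same rule, and match the predictor count in Study Sample Size Determination to it.
5. State a fallback for sparse data, since few men are expected: for example, omit the gender term from a logistic model in which it cannot be estimated. With at most 60 observations, keep the logistic models to the smallest pre-specified set.
6. Say explicitly whether application usage stays in the main model. The article now fixes it in all models. Whether it belongs there is a separate question, and it should not be dropped silently.

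The cost is a change of wording. It needs no new data and no change in sample size. The one downside is a weakly estimated gender term if men are few, which the fallback covers.

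### The choice between complete-case analysis and multiple imputation is left open until missingness is seen, under example triggers that do not bind the team or name arm or the 3-month score

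*Protocol article*

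**What the plan says.** Under Statistical Analysis, Quantitative Analysis, the Protocol article says: "The proportion of missing data will be examined before outcome analyses" in order "to determine whether a complete case analysis is appropriate or whether multiple imputation is warranted". Its triggers for imputation are: "eg, if there is a large proportion of missing data, ie, >5%; if there are patterns in missingness based on demographic factors". It does not say whether the 5% is counted per item, variable, visit or participant. Retention is to be described by completion rates. Baseline stress and caregiver mental health are compared between arms, but as a check on randomization and not on dropout.

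Under RAISE Effectiveness, the outcome regressions contain arm, the baseline level of the outcome, app usage and demographic characteristics. The 3-month score is not listed as a term in 6-month models. The same section states an intent-to-treat design in which "all initially assigned to the intervention group are included in analyses, whether or not they used the intervention".

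Study Sample Size Determination plans "a planned enrollment of 30 participants per study arm", gives power "for primary analyses considering a sample of 60 participants with α=.05", and says that effect size will be cautiously considered when sizing a later efficacy trial.

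**The concern.** The rule decides which analysis is primary, yet it can be read in several ways. Because the triggers are examples, a team with 8% missing is not bound to impute. Counted per variable or per visit, the 5% could be passed on one outcome and not on another.

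The missingness most likely to distort a comparison of arms is missingness that differs by arm and follows how caregivers are doing. A caregiver who is still highly stressed at 3 months with a self-guided app may skip the 6-month survey for reasons that do not apply to someone given a brochure. The 3-month score would then carry the information needed to correct the 6-month comparison. A complete-case regression on arm and baseline does not use it. Imputation from the same covariates does not use it either.

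At stake is the 6-month effect estimate, which may help to size the next trial.

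**Working it through.** **The plan's own power figure.** Inputs from Study Sample Size Determination: N = 60, α = .05, 4 predictors, "estimating a medium effect size (Cohen f^2^=.15), power=.62". For the overall F test, df1 = 4, df2 = 60 − 4 − 1 = 55 and noncentrality 0.15 × 60 = 9. Power is 0.621, so the stated .62 reproduces. It uses all 60 caregivers. The same test gives 0.593 at N = 57, 0.564 at N = 54 and 0.503 at N = 48.

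**What a strict 5% rule allows.** Counted over participants, 0.05 × 60 = 3, so imputation starts at 4 missing. No dropout rate is stated, so a range is assumed. The chance that imputation is triggered is P(X > 3), with X binomial(60, d):

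| Dropout d | P(more than 3 missing) |
|---|---|
| 2% | 3% |
| 5% | 35% |
| 8% | 72% |
| 10% | 86% |
| 15% | 98.5% |
| 20% | 99.9% |

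With 10% missing in one arm of 30 and 26% in the other, the expected number missing is 3 + 7.8 = 10.8 (18%), and the chance of more than 3 is 99.7%.

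**Bias at 6 months when dropout follows the 3-month score.** Simulation assumptions:
- no true effect, 30 per arm;
- baseline-outcome correlation .5, 3-to-6-month correlation .7;
- brochure arm 10% missing at random;
- RAISE arm about 26% missing, with the chance of being missing rising with 3-month stress.

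The estimate is the arm coefficient from a regression of the 6-month score on arm and baseline. Negative values favor RAISE.

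| Analysis | Mean bias (SD) |
|---|---|
| Complete case, weaker dependence on 3-month stress | −0.108 |
| Complete case, stronger dependence | −0.136 |
| Complete case, repeat runs over several strengths | −0.10 to −0.15 |
| Imputation from arm and baseline only | same as complete case |
| Imputation that also uses the 3-month score | about 0.00 |

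The fourth row has a simple reason: values imputed from arm and baseline lie, in expectation, on the fitted complete-case regression, so refitting returns the same coefficient. Regression imputation was used throughout as the expected value of multiple imputation.

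**Bias if the cut-off is applied strictly.** Use complete cases at 3 or fewer missing, and imputation with the 3-month score above that. The average bias is then about 0.02 SD or less. Two single cases with exactly 3 missing show the scale. Two RAISE caregivers weighted toward high 3-month stress plus one random brochure caregiver give about −0.04 SD. The three highest 3-month scorers in RAISE give about −0.09 SD.

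**Scale.** The standard error of the arm effect with full data is about √[(2/30)(1 − 0.5²)] = √0.05 = 0.22 SD. A bias of 0.11 to 0.15 SD is therefore 0.5 to 0.7 of a standard error.

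**Can inspection settle it?** At 30 per arm, a test for unequal missingness has power of about .50 for 10% versus 30% and .20 for 10% versus 20%. With 3 missing, all in one arm, Fisher's p = 2 × C(30,3)/C(60,3) = 8120/34220 = 0.24. Finding no pattern is weak evidence that there is none.

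**Where the choice matters less, or imputation does not rescue it.** In a separate simulation (correlation .6, about 19% missing, stress-driven dropout in RAISE only), complete-case bias is about 0.00 SD when dropout depends on baseline stress, because the model adjusts for it. It is about −0.15 SD when dropout depends on the 6-month score itself. Standard imputation, which assumes missing at random, would not remove that last bias in full.

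**The case against.** The strongest reply is that the 0.11 to 0.15 SD arises at about 18% missing, where the plan's own cut-off points to imputation in 99.7% of trials. Where complete-case analysis survives a strict reading, at most 3 caregivers are missing and the choice hardly matters. This stands. The larger figure holds only if the example rule is applied loosely, or if imputation leaves out the 3-month score.

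Three stronger readings are tempting, and the documents do not support them.
- A reader might infer that only demographic patterns will be checked. The triggers are examples, so checks by arm or by stress are not ruled out; they are merely not named.
- A reader might infer that the method can be chosen by its result. The text places the check before the outcome analyses and bases it on missingness.
- A reader might infer that complete-case analysis contradicts the intent-to-treat statement. That statement is framed by app use and does not address caregivers without outcome data. It is a gap, not a contradiction.

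It is also fair that the imputation model and sensitivity analyses may sit in an analysis plan that is not shown. Their absence from the article is not the complaint. The complaint is that the rule the article does state leaves the primary method undecided. The trial is an acknowledged, underpowered pilot, which limits the consequences without removing them.

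**Conclusion.** The point holds as a weakness in how the primary missing-data method is fixed. On a strict reading with a well-built imputation, the expected bias is about 0.02 SD or less. On a loose reading, or with imputation from the regression's own covariates, a false 6-month benefit of about 0.11 to 0.15 SD is possible. That range rests on assumed correlations of .5 and .7, on 10% versus 26% missing, and on RAISE dropout that follows 3-month stress. The documents give none of these figures. It would be wrong to conclude that the plan will produce this bias, or that dropout linked to baseline stress goes unhandled: the planned baseline adjustment largely deals with it. The change is worth making because it costs little and removes discretion over an estimate that may help to size the next trial.

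**What to change.** Replace the switch with one primary approach, stated before outcome data are analysed, for all randomized caregivers in both arms. Either of these would serve:
- multiple imputation with arm, the baseline value and, for 6-month analyses, the 3-month value of the outcome in the imputation model; or
- for continuous outcomes, one longitudinal model of the 3- and 6-month scores with baseline as covariate.

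Report complete-case results as a sensitivity analysis and tabulate missingness by arm. Extend the intent-to-treat sentence to both arms and to caregivers with missing outcomes. With the switch gone, the 5% threshold and its denominator are no longer needed.

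Cost: a change of wording and a little more analysis work. If 3 or fewer caregivers are missing, the extra work will hardly change the answer.
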